### Outline of data collection

To address Aim 1, preliminary data collection was necessary to inform the specific instruments and supplementary questions that would be administered to traumatic injury patients. First, an online survey was sent to Wisconsin trauma center medical directors and trauma coordinators to gather information on current substance use screening practices. Details regarding the procedures and results of these activities are attached in Additional file 1: Online Supplement 1. Next, a focus group of Wisconsin trauma center staff was convened to discuss barriers and facilitators to screening, resources available and needed to support trauma patients at risk for opioid use disorders, and measurable clinical observations that could indicate a patient’s potential risk for opioid misuse. Details regarding these procedures and results are attached in Additional file 2: Online Supplement 2. Finally, these data were used to finalize the items that are currently being administered to inpatients receiving trauma services (n = 295) at an ACS Level-1 trauma center in Wisconsin. In turn, these data will be analyzed and used for the development and validation of a screening tool for opioid use disorder risk after traumatic injury. The screening tool will be pilot-tested at four ACA Level-I and Level 2 II trauma centers in Wisconsin.

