### Statistical analyses

#### Aims 1 and 2: sample size calculations

Based on an expectation of an at-least 8% incidence in the sample over 24 weeks observation of opioid misuse or an opioid use disorder diagnosis, 221 participants would yield 80% power, at a 5% significance level, with a logistic regression to detect an odds ratio of 2.0 for a change of one standard deviation (SD) in score on the COMM. With a 25% drop-out rate expected, the study aims to recruit a total of 295 participants. While the current proposed work will not be adequately powered to attain significant findings regarding predictors of opioid overdose, examination of this outcome will constitute an exploratory aim.

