#### Aims 1 and 2: analysis

The primary outcome event of this study will be a composite outcome indicating the development or lack of opioid misuse or opioid use disorder within 24 weeks of hospital discharge after traumatic injury. To assess the associations between patient factors and hypothesized risk factors with primary event, t-tests, Wilcoxon rank sum tests, and Chi square tests will be applied to measures that differ between those participants who achieve the primary event and those who do not. The test that is used will be based on numeric (normal or non-normal distribution) or a categorical factor. Any baseline or week 4 variable that is univariately associated with the primary event (p < 0.05) and does not reduce the number of events by more than 5% due to missing data will be considered a candidate variable to be included in the development of a best fit prediction model. The prediction model will be constructed based on a forward step-wise logistic regression model building process with threshold for entry into the model of significantly improving the model at a 0.05 significance level. Including baseline and week 4 variables will allow knowledge of which baseline variables are associated with future opioid misuse or opioid use disorder, and which variables can indicate the beginning of addiction in the hopes to develop a method to intervene before the onset of opioid misuse or opioid use disorder. To control for a possible early drug effect, time-on-opioids will be used as a covariate in the model. The diagnostic ability of the model will be assessed by constructing a receiver operating characteristic (ROC) curve and calculating the optimal sensitivity and specificity to predict primary event based on Youden’s J statistic [34]. A secondary survival analysis will examine variables that are associated with time-to-event, such as overdose or incident misuse detected on study measures.

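### The article promises development and validation of the screening tool on one cohort, but its only stated accuracy assessment is made in the participants used to select the model and set the cut-off

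*Protocol article*

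**What the plan says.** In *Outline of data collection*, the article says that the data from the 295 inpatients will be "used for the development and validation of a screening tool for opioid use disorder risk after traumatic injury".

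*Aims 1 and 2: analysis* sets out how. Baseline and week 4 variables become candidates if they are univariately associated with the outcome at p < 0.05 and if their missing values do not cost more than 5% of the events. The model is then built by a "forward step-wise logistic regression model building process with threshold for entry into the model of significantly improving the model at a 0.05 significance level", with time on opioids as a covariate. Performance comes next: "The diagnostic ability of the model will be assessed by constructing a receiver operating characteristic (ROC) curve and calculating the optimal sensitivity and specificity", with the optimum defined by Youden's J.

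The expected number of events follows from *Aims 1 and 2: sample size calculations*, which assumes an "at-least 8% incidence in the sample over 24 weeks observation" and states that "221 participants would yield 80% power, at a 5% significance level, with a logistic regression" for an odds ratio of 2.0 per SD of one score, the COMM.

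For the pilot, *Aim 3: analysis* lists RE-AIM outcomes: patients reached, patients screened and followed up, providers involved, coaching dose and adaptations.

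**The concern.** The screen, the forward selection and the choice of cut-off are all tuned to the outcome in this cohort. Reading AUC, sensitivity and specificity from the same cohort measures how well the tool describes the data that shaped it, not how well it will classify the next patient. The gap is largest when events are few and candidates many, which is the position at the planning incidence.

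Aim 3 does not close the gap. It counts who is screened and followed up; it does not ascertain misuse or opioid use disorder in screened patients, so accuracy is never checked in new patients. The published sensitivity would be the figure a trauma centre relies on to judge how many at-risk patients the tool finds. If it reads about 0.75 when the value in new patients is about 0.50, the tool misses about half of them while the report suggests a quarter.

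**Working it through.** **1. The plan's own sample size.** Inputs: incidence 8%, odds ratio 2.0 per SD, 80% power, 5% significance (taken as two-sided), 25% drop-out. For one continuous covariate in logistic regression,

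n = (z(0.975) + z(0.80))² / [p(1 − p)(ln OR)²] = 7.849 / (0.0736 x 0.4805) = 221.96.

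This reproduces 221 (truncated); power at 221 is 79.8%. Recruitment is 221 / 0.75 = 294.7, so 295. The calculation covers one standardised predictor. It does not address selection among many, or the precision of sensitivity and specificity.

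**2. Events.** 221 x 0.08 = 17.7, about 18. This is a floor, because the article expects at least 8%.

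**3. Candidates.** Counting from *Independent variables*, *Administrative data sources* and Table 1: 8 sociodemographic items, 9 baseline instruments or dose measures, 5 injury or clinical items, the Injury Severity Score, and 9 week 4 measures give 8 + 9 + 5 + 1 + 9 = 32. Counting the two PROMIS domains separately makes 33. COPE domains and PCS subscales would add more. Events per candidate are 17.7 / 33 = 0.54.

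**4. Size of the optimism at 8% incidence.** Simulated trials with n = 221: t-test screen at p < 0.05, forward likelihood-ratio entry at 0.05, ROC curve, Youden cut. The fitted model and cut were then applied to 20,000 new patients. Candidate counts and true effects are assumptions; predictors are normal.

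| Assumed truth | Candidates | AUC, same data → new | Sensitivity | Specificity |
|---|---|---|---|---|
| One predictor, OR 2.0 | 20 | 0.74 → 0.63 | 0.73 → 0.49 | 0.70 → 0.68 |
| One predictor, OR 2.0 | 40 | 0.77 → 0.60 | 0.77 → 0.44 | 0.71 → 0.69 |
| ORs 2.0, 1.5, 1.5; correlation 0.2 | 20 | 0.78 → 0.70 | 0.78 → 0.55 | 0.72 → 0.71 |
| ORs 2.0, 1.5, 1.5; correlation 0.2 | 40 | 0.80 → 0.67 | 0.79 → 0.50 | 0.74 → 0.72 |
| One OR 2.0, or three OR 1.5; correlation 0.3 | 33 | 0.73-0.77 → 0.62-0.66 | 0.75-0.77 → 0.49-0.51 | gap about 0.02 |

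In the 33-candidate row the gaps are about 0.11 for AUC (0.77 − 0.66) and 0.26 for sensitivity (0.77 − 0.51). Adding the article's missing-event rule, with 5% missingness per item assumed, barely changes them. With one predictor at OR 3, the AUC gap is about 0.06.

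**5. Dependence on incidence.** 30 candidates; first figure for one OR 2.0 predictor, second for ORs 2.0, 1.5, 1.5.

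| Incidence (events) | AUC gap | Sensitivity gap | Specificity gap |
|---|---|---|---|
| 16% (35) | 0.07, 0.06 | 0.17, 0.16 | 0.02, 0.03 |
| 30% (66) | 0.05, 0.05 | 0.11, 0.09 | 0.04, 0.04 |
| 42% (93) | 0.04, 0.03 | 0.06, 0.06 | 0.06, 0.04 |

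The 42% row is the misuse rate that the Background cites for emergency room patients. With 33 candidates the AUC gap is 0.05-0.07 at 16% and 0.03-0.06 at 30%.

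**6. Precision.** Leaving optimism aside, an observed sensitivity of 14/18 has an exact 95% interval of 0.52 to 0.94.

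**7. Does the remedy work?** In 60 simulated trials with 40 resamples each, bootstrapping the whole procedure gave a corrected AUC of 0.670, against 0.661 in new patients and 0.762 in the same data.

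**The case against.** The strongest reply is that this is a condensed article. Resampling details usually sit in a full protocol or analysis plan, nothing in the text rules them out, and the word validation may signal that some are planned. That is fair as far as missing detail goes. It does not dispose of the point: the article claims validation and, in the section that should deliver it, specifies an assessment that is biased if followed as written. Cross-validation, or dropping the word validation, would also remove the contradiction.

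Four stronger readings are tempting, and the documents do not support them.

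- *All the accuracy figures will be badly overstated.* Specificity is overstated by only about 0.02 at 8% incidence. Eight per cent is also a floor: the composite includes any COMM score of 9 or more at week 24, and with more events the AUC gap shrinks to a few hundredths.
- *A worthless tool would usually look useful.* With no true predictor, a model emerges in about 69% of simulated trials with 33 candidates, but in only about 49% once the missing-event rule is applied with 5% missingness. With 18 events, one missing value is 1/18 = 5.6%, enough to exclude a variable. The article also cites known predictors, so a complete null is unlikely.
- *The optimism is the same whatever the predictors.* Week 4 COMM is a candidate for an outcome partly defined by week 24 COMM. A strong predictor of that kind reduces the AUC gap.
- *The figures will justify a roll-out.* The article describes an implementation pilot and makes no accuracy threshold a condition for it.

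**Conclusion.** The point holds in this form. Validation is claimed for the cohort, the only stated performance assessment is in the development sample, and Aim 3 supplies no outcome on which accuracy could be checked. At the planning floor of about 18 events, AUC is overstated by about 0.10 and sensitivity by about 0.25, with specificity little affected. Both gaps narrow as incidence rises, and the AUC gap narrows if one predictor is strong, but some optimism remains in every scenario examined that had a true signal.

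The direction of the bias follows from the procedure itself. The sizes rest on assumptions: 20 to 40 candidates, odds ratios of 1.5 to 2.0 per SD, independent or mildly correlated normal predictors, and no time-on-opioids covariate in the simulation. They should be read as orders of magnitude.

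**What to change.** In *Aims 1 and 2: analysis*, add internal validation of the whole procedure. In each bootstrap resample (or each fold of a repeated cross-validation), rerun the univariate screen with its missing-data rule, the forward selection and the Youden cut. For the bootstrap, apply the resulting model and cut to the original sample, average the loss in performance over resamples, and subtract it from the same-data figures. Report optimism-corrected AUC, sensitivity, specificity and calibration slope, with confidence intervals, as the headline results. Shrinking the coefficients before converting them to item scores is optional.

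In *Outline of data collection*, change the description to development and internal validation. If no internal validation is to be done, remove the word validation.

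The cost is a few hours of programming and some wording. No further patients are needed. The reported performance will be less favourable.

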#### Aim 3: analysis

Aim 3 analysis will involve mixed methods. Formative evaluation will inform the implementation model, based on pre-implementation stakeholder interviews. Quantitative evaluation of the implementation process is based on the Reach, Effectiveness, Adoption, Implementation, Maintenance (RE-AIM) model [35]. The following outcomes will be assessed pre-post implementation in pilot test sites: (1) Reach: Number and characteristics of patients served in pilot trauma centers compared to patients of trauma centers nationally; (2) Effectiveness: number and percentage of trauma patients screened and receiving follow-up; (3) Adoption: number and characteristics of providers conducting screening/follow up with patients; (4) Implementation: number and characteristics of providers participating in the coaching intervention; intervention “dose” received; and adaptions made to the implementation model for each site. Assessing the dose of intervention received will be defined as the number of coaching hours delivered to clinic staff, and tracked by coach logs. To measure adherence, the planned protocol will be reviewed with clinicians and site staff, and adaptations made to the protocol at each site will be documented and reviewed. Quality of the intervention delivery will be assessed by asking clinicians to reflect on their experience with peer coaching, and the effect it had on their attitudes about opioid prescribing. Providers and hospital staff who were involved with peer coaching will be invited to participate in a focus group, which will explore the kinds of workflow changes that were associated with successful implementation, what factors helped staff make changes, what factors acted as barriers to change and how those barriers were addressed, and what aspects of implementation did not work well. Focus groups will also seek to compare the experience of clinicians at sites that successfully implemented the opioid screening protocol into their workflow compared to those at sites that did not.

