### Pilot implementation of the risk screening tool

Study Aim 3 relies upon a well-established approach to the implementation of evidence-based practices, based on fundamental principles of organizational change developed by the Network for the Improvement of Addiction Treatment (NIATx) [28–30]. Of the approaches used to deliver the NIATx organizational change model, peer coaching has emerged as the most cost-effective option [28]. Members of the research team have adapted the peer coaching model employed by NIATx and applied it to promoting adoption of clinical guidelines for opioid prescribing in primary care [31]. Further adaptations will be made to tailor the approach for trauma settings. Peer coaches guide organizations through the change process by assessing workflows and identifying opportunities for improvement, and facilitating the plans, actions, analysis, and adoption of those improvements. This study will culminate with the pilot test of a strategy for implementing an opioid risk screening protocol in Wisconsin’s 4 largest trauma centers, using the novel opioid risk screening that was developed from the trauma patient data.

Implementation work will begin with observations of the UW Hospital Trauma Inpatient Service clinical workflows regarding the Alcohol Use Disorders Identification Test (AUDIT-C), a standardized alcohol use screening tool, a process which will inform potential implementation procedures for the opioid risk screen [32, 33]. This observation period will focus on when, where, and who is administering the AUDIT-C, how the information obtained from the AUDIT-C is recorded and communicated to the clinical care team, if and how that information guides clinical care decisions, and if and how an intervention or referral to treatment is conducted with the patient. Interviews will be conducted with UW Hospital Trauma Inpatient Service staff to assess how opioid risk screening could fit within the trauma inpatient workflow and how opioid-related interventions might best dovetail with that workflow. Nuances of the implementation model that are specific to a trauma service will be shared from the UW site to the four other pilot testing sites. The implementation model will be continuously refined based on the experience of each subsequent implementation, with emphasis placed on adjustments that are needed to tailor the implementation model for local organizational contexts.

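### Aim 3 reports coach-hours delivered under the name of dose received, and its delivery-quality assessment names no attitude to the opioid risk screening being implemented

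*Protocol article*

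**What the plan says.** The section Aim 3: analysis in the protocol article sets out outcomes under the RE-AIM model. The Implementation item includes the "number and characteristics of providers participating in the coaching intervention", the dose of intervention received, and the adaptations made at each site. The dose is then defined: "Assessing the dose of intervention received will be defined as the number of coaching hours delivered to clinic staff, and tracked by coach logs".

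Delivery quality has two elements. The first is stated as "Quality of the intervention delivery will be assessed by asking clinicians to reflect on their experience with peer coaching". The second is "the effect it had on their attitudes about opioid prescribing".

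The section Pilot implementation of the risk screening tool describes Aim 3 as a "pilot test of a strategy for implementing an opioid risk screening protocol". It says that the research team had adapted the peer coaching model and "applied it to promoting adoption of clinical guidelines for opioid prescribing in primary care". It adds: "Further adaptations will be made to tailor the approach for trauma settings".

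**The concern.** There are two mismatches, both in what the article states.

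- **Dose.** The outcome is named for what staff received, but the measure is what the coach supplied, taken from the coach's own log. Ten hours spent with one coordinator and ten hours spent with twenty clinicians score the same.
- **Quality.** The coaching is there to bring a screening protocol into use, yet the one attitude asked about concerns prescribing.

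At stake is how the pilot will be read. The Discussion names an implementation strategy as one of the project's three products, and the focus groups are to compare clinicians' experience at sites that did and did not take up the screen. If a site does not take it up, the team will want to know whether its staff had little coaching, or had plenty and still did not adopt. Coach-hours alone cannot separate these two cases. Likewise, an answer that coaching left prescribing attitudes unchanged would not say whether attitudes to screening had moved.

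**Working it through.** The plan gives no figure for coaching hours or attendance, so there is nothing to reproduce. The check is on the definitions, and all numbers below are assumed for illustration.

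**Step 1: coach-hours alone.** Take two sites with 10 coach-hours each, one with 2 people at every session and the other with 15.

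- Dose as defined: 10 at both sites.
- Person-hours attended = hours × attendees: 10 × 2 = 20 and 10 × 15 = 150.
- Ratio: 150 / 20 = 7.5.

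**Step 2: add the provider count.** The Implementation item also reports how many providers took part. If the same people attend throughout, that count (2 against 15) does separate the two sites in Step 1. So the question is whether hours and headcount together settle exposure in general.

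Take one site report of 10 one-hour sessions and 15 participating providers.

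- Lowest case, each provider attends one session: 15 × 1 = 15 person-hours.
- Highest case, every provider attends every session: 15 × 10 = 150 person-hours.
- Ratio: 150 / 15 = 10.

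The same reported pair fits both. Average exposure is 1 hour per provider in the first case and 10 hours in the second. Attendance by session is needed to tell them apart, and the stated definition does not use it.

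**Step 3: set the quality items against the target of the coaching.**

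| Element | Subject |
|---|---|
| What the pilot implements | Opioid risk screening protocol |
| Effectiveness outcome | Patients screened and receiving follow-up |
| Adoption outcome | Providers who screen and follow up |
| Quality, first element | Experience with peer coaching |
| Quality, second element | Attitudes to opioid prescribing |

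The first quality element is general and may draw out comments on screening. The second is specific, and it is specific to prescribing. No element names attitudes to screening. The prescribing wording matches the earlier primary-care use of the coaching model, but that it was carried over from there is only an inference.

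**Step 4: is the prescribing item out of place?** No. The Discussion says that trauma centers will be encouraged to use certain precautions for patients who screen positive, and it links those precautions to safer opioid prescribing. Prescribing attitudes are therefore relevant downstream of a positive screen. The quality assessment is incomplete, not misdirected.

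**The case against.** The strongest case against the point has four parts.

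1. **Coaching is aimed at organizations.** The article says that peer coaches guide organizations through change, so hours delivered to a site's staff is a coherent site-level dose. Person-hours also has a weakness: it ranks a large passive meeting above intensive work with a small change team. This stands, and it is a reason to keep coach-hours and report person-hours beside them. It does not make hours delivered a measure of dose received.
2. **Log contents are operational detail.** A condensed article may leave these to the full protocol, and the logs may already hold attendance. That is possible. The point rests on the definition that the article does state, not on what it leaves out.
3. **The provider count already covers reach.** It does so in part, as Step 2 shows, but it does not give exposure.
4. **No quantitative analysis uses dose.** The comparison of sites is a qualitative one through focus groups, and no dose-response or exposure-adjusted analysis is stated. This stands, and it limits the weight of the point.

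A reader might go further and infer that Aim 3 cannot show whether the coaching worked, or that delivery quality is judged by prescribing attitudes alone. The document supports neither reading. Success is assessed elsewhere: by the number and percentage of patients screened and followed up (Effectiveness), by the providers doing the screening (Adoption), both before and after implementation, and by focus groups that ask what did not work. Dose and quality are process measures and are not meant to carry that conclusion. The quality assessment also begins with clinicians' experience of peer coaching.

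**Conclusion.** The point holds in a limited form. The measure defined for dose received is dose delivered, and with the provider count added it still does not show how much coaching staff at a site received. In the assumed example, the same reported hours and headcount cover a tenfold range of exposure. The size depends on the assumed sessions and attendance; if everyone attended everything, hours and headcount would be enough. The quality assessment omits attitudes to the screening that the coaching is meant to implement, while its prescribing question is relevant and should stay.

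This is a minor improvement to a descriptive four-site pilot aim. It changes no stated decision rule, and it leaves the primary outcome, the sample size for Aims 1 and 2 and the prediction model untouched.

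**What to change.** - Report coach-hours as dose delivered, at site level.
- Add two fields to the existing coach log: attendees by role, and session length. Report person-hours attended as dose received, alongside coach-hours.
- Add a question on how coaching affected clinicians' attitudes to, and practice of, opioid risk screening and follow-up. Keep the prescribing question and the general question on the coaching experience.

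The cost is a slight recording burden for coaches and one more question for clinicians. No current measure is lost. The log change should be in place before coaching starts, because attendance is hard to reconstruct afterwards.
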